## Abstract

Individual and group cardiac rehabilitation (CR) programs reduce cardiovascular morbidity and mortality by reducing recurrent events, improving risk factors, aiding compliance with drug treatment, and improving quality of life through physical activity and education. Home-based programs are equally effective in improving exercise capacity, risk factors, mortality, and health-related quality of life outcomes compared to hospital-based intervention. Cardio-telerehabilitation (CTR) programs are a supplement or an alternative to hospital rehabilitation programs providing similar benefits to usual hospital and home care. Despite this statement, implementation in the public and private healthcare environment is still scarce and limited. The main objective of this research was to evaluate the efficacy, feasibility, and adherence of a personalized eight-week mHealth telerehabilitation program in low-risk cardiac patients in the hospital of Melilla (Spain). The secondary aims were to investigate patient satisfaction, identify barriers of implementation and adverse events, and assess cost-effectiveness from a health system perspective. A study protocol for a single center prospective controlled trial was conducted at the Regional Hospital of Melilla (Spain), with a sample size of (*n* = 30) patients with a diagnosis of low-risk CVD with class I heart failure according to NYHA (New York Heart Association). Outcomes of this study, will add new evidence that could support the use of CTR in cardiac patients clinical guidelines.

## 1. Introduction

Effective secondary prevention programs have great potential to reduce the burden of cardiovascular disease (CVD). The *Global Burden of Disease* (GBD) study, published in 2018, revealed the worrying dimension of the CVD pandemic [1]. CVD caused one third of all deaths in 2015, with an estimated prevalence of 422 million cases, predominantly atherosclerotic, cardiovascular disease (coronary heart disease and stroke) [1]. In recent decades, CVD mortality rates have fallen in developed regions. Improvements in cholesterol levels, blood pressure and smoking are responsible for 44% of the decline, while 47% of the decline is due to evidence-based medical care, therapies, and surgery [2]. The American Heart Association (AHA), proposed and developed a new metric of ideal cardiovascular health index as a means of assessing the cardiovascular health of a population, in what they called “LS7” (Life simple seven). The system is based on the ideal values of seven cardiovascular risk factors and health behaviors, all of which are modifiable. The LS7 score includes seven risk control factors, including three health factors (blood pressure BP, total cholesterol, and blood glucose) and four health behavioral factors (body mass index (BMI), smoking, physical activity, and diet) [3].

Individual and group cardiac rehabilitation (CR) programs, reduce cardiovascular morbidity and mortality by reducing recurrent events, improving risk factors, aiding compliance with drug treatment, and improving quality of life through physical activity and education [4]. According to the clinical practice guidelines for stable cardiovascular patients of the European Society of Cardiology (ESC), secondary prevention through a cardiac rehabilitation program is highly recommended [4]. A recent Cochrane systematic review with meta-analysis including 12 articles, concluded that home- and center-based forms of cardiac rehabilitation seem to be equally effective in improving clinical and health related quality of life outcomes in cardiac patients [5]. Unfortunately, despite these benefits and recommendations, many heart patients do not participate in group or individual cardiac rehabilitation (CR) programs. According to the EUROASPIRE questionnaire, only 44.8% of patients after a coronary event or revascularization stated that they had been advised to attend CR programs, and of these, only 81.4% had attended CR programs (36.5% of all patients) [6].

A recent systematic review collecting evidence published between 2001 and 2016 suggested that cardiac rehabilitation is cost-effective, especially with physical exercise as a major component [7].

Moreover, economic evaluations of health interventions, provide important information to health care providers, patients, planners, and politicians on the availability of alternatives in the context of limited resources [8]. The World Health Organization (WHO) recommends the use of the value-for-money threshold to identify the cost-effectiveness of an intervention [9]. The American College of Cardiology (ACC) and the American Heart Association (AHA) recommended a more recent guideline for the evaluation of interventions in cardiac patients. This “value for money” for health is generally identified as ‘very good’, ‘relatively good’, or ‘not good’ [10]. The absence of major differences in the costs of a home versus hospital-based CR programs, as found in the 2015 Cochrane review by Taylor et al., support the continued expansion of home cardiac rehabilitation programs [11].

The European Society of Preventive Cardiology recommends the inclusion of cardiac telerehabilitation (CTR) programs as novel intervention strategies. They identify CTR as a supplement or an alternative to hospital programs [12]. Telerehabilitation (TR) programs for patients with heart conditions provided similar benefits to usual hospital and home care, with no adverse effects reported according to a recent systematic review in 2016 [13]. Telerehabilitation is a term used to describe the provision of rehabilitation services at a distance, using communication technologies [14]. The Global Observatory for eHealth defined mHealth or mobile health as medical and public health practice supported by mobile devices, such as mobile phones, patient monitoring devices, personal digital assistants, and other wireless devices [15]. Mobile technology also has the potential to overcome barriers in performing cardiac rehabilitation monitoring, becoming a useful tool to promote compliance. Studies have shown that the use of mobile health interventions has positive benefits in increasing participation in rehabilitation [13]. 

Despite the fact that CTR has been shown to be as effective as CR in the hospital and home environment in terms of exercise capacity and quality of life, to be cost-effective and to improve patient satisfaction and adherence, its implementation in the public and private healthcare environment is still scarce and limited [4,16,17]. Considering the current health era and the large number of patients with cardiovascular diseases, it is advisable to carry out feasibility, safety, and effectiveness studies in the implementation of cardiac telerehabilitation programs both in the hospital environment and in other areas of care.

The aim of this research was to evaluate the efficacy, feasibility, and adherence of a telerehabilitation program in low-risk cardiac patients in the hospital of Melilla (Spain).

The secondary aims of this trial were to investigate patient satisfaction, to identify barriers of implementation and adverse events, and to assess cost-effectiveness from a health system perspective (costs of health interventions).

## 2. Material and Methods

This piece of research is a single center prospective controlled trial conducted at the Regional Hospital of Melilla (Spain), which will facilitate voluntary participant recruitment and the supervised CTR program component.

This research involves the departments of Cardiology, Rehabilitation, Physiotherapy, and Research at the University of Granada. All CTR staff will receive training on how to integrate the intervention training. As this study runs parallel to clinical practice, all medical management, including medication prescription, will be at the discretion of the treating physician. All changes will be documented and considered during analysis. 

This research uses the guidelines on Standards for Quality Improvement and Excellence in Reporting (SQUIRE) [18] and will be carried out in accordance with CONSORT (Consolidated Standards of Reporting Trials) criteria [19]. A Standard Protocol Items Recommendations for Interventional Trials (SPIRIT) checklist is provided as Supplementary File S1, and the flow diagram for the study protocols is included as Figure 1.

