### 2.2. Intervention

Participants are assigned to the cardiac telerehabilitation group to receive an initial assessment. The CTR group receives a personalized 8-week exercise program through a mHealth application that allows health professionals to generate videos, images, and parameters of each exercise, as well as send them by email, instant messaging, and follow up on patients. In this study, we use the Physiotec exercise prescription app as it allows us to create personalized CTR programs according to particular clinical case and follow their progress. The CTR program describes the exercises to be performed, the number of repetitions according to the level of training and the criteria for progression. The CTR program includes aerobic exercise at 60–85% of the maximum heart rate (HR) reached in the ergometry test. As patients are taking β-blocker drugs, they will never reach their maximum HR. Patients will be instructed in the use of the Modified Borg Scale to assess their level of fatigue while performing the CTR program. Exercises customized to each participant should be performed between values 4–6 on this scale (out of a maximum of 10).

The type of exercise can be continuous or intervallic (load or HR controlled):

Continuous Exercise: After an initial warm-up period of 5–10 min, the patient is brought into a phase where he or she remains at a HR or resistance previously determined by the intervention team.

Interval Exercise: After an initial warm-up period, an exercise is started which alternates load peaks with lower intensity ones.

All patient training sessions should end with a return to the initial baseline situation (relaxation phase) of similar duration to the warm-up phase 5–10 min.

Typical CTR training session: -Control of basal constants (by the patient): HR, blood pressure, weight, blood sugar…-Permanent monitoring during the whole CTR session (patient must understand and follow the modified Borg scale as well as to use activity bracelets, pulse meters, or other monitoring instruments)-Exercise session:
∘Initial warm-up: 5–10 min (follow-up the video exercises provided through the CTR tool).∘Aerobic training: 35–45 min (follow up the video exercises provided through the CTR tool)∘Return to calm, relaxation-cooling: 5–10 min (follow up of the video exercises provided through the CTR tool)∘Recording of incidents and patient feedback in the CTR tool. Patient/physiotherapist feedback

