Patients are initially supervised by the research team who will conduct 1-to-1 training sessions to ensure proper execution of the exercises and encourage patient adherence. Patients are instructed to perform self-training by following the video exercises through the CTR program. At the beginning of the study, advice is given on general care, in physical activity and issues concerning drug intake.

Patients are advised to refrain from any other specific training during the intervention period. Any deviations from the adherence and practice of the CTR program are recorded daily, noting any adverse incidents.

The TR group receives a personalized program for 8 weeks, including at least one session per day and is done through a web and mobile application. The telerehabilitation application allows health professionals to create personalized exercise programs, hold video conferences with patients, generate videos, images and parameters of each exercise, as well as send them by email and follow up patients through the mobile application.

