### 2.5. Statistical Analysis

This research is a single center prospective controlled trial pre/post design. The results of the trial research will be presented as a summary of the outcome measures, together with the estimated effect size and precision. Statistical analysis will be performed according to the intention-to-treat principle. Patient characteristics will be summarized using frequencies and percentages for categorical factors, and using means and standard deviations for continuous measures in order to have as much information as possible available for exploration and analysis. The effect sizes will be calculated using Cohen’s d, so that the results can be compared to other studies. The outcome measures will be compared before and after the completion of the 8-week CTR program. All statistical analyses will be conducted using SPSS software. Statistical significance was set at *p* < 0.05.

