## 3. Results

Enrollment began in February 2021. First study results will be reported in the middle of 2021. Recruitment is currently underway. The recruitment goal is 30 cardiac rehabilitation patients. Data collection is anticipated to be complete by July 2021.

If the results confirm beneficial effects in biochemical, cardiac function, quality of live, and functional capacity, the effectiveness of the intervention will be proven in patients with heart failure. The successful delivery of the intervention, the absence of significant adverse effects, and the user satisfaction will demonstrate the feasibility of these interventions in cardiac patients.

The results of this study will determine if a larger-scale intervention is feasible. Further, this pilot study will be the first to examine the effect of CTR intervention on patients in a cardiac rehabilitation setting in Melilla (Spain). The results of this study will provide differences compared to previous research: first of all, its implementation in the autonomous city of Melilla (located on the African continent with particular demographic characteristics); secondly the use of the innovative CTR platform based on the App Physiotec; thirdly, the collection of outcomes that combine clinical, self-reported and economic data and lastly, automated treatment adherence registry.

This study will add more evidence in support of the use of CTR program as an effective tool in new cardiac rehabilitation programs.

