## Figures and Tables

**Figure 1 ijerph-18-04038-f001:**
[figure not shown]
Study design. Abbreviations CVD, cardiovascular disease; CTR, cardio-telerehabilitation.

**Table 1 ijerph-18-04038-t001:** Inclusion and exclusion criteria.

Inclusions Criteria	Exclusions Criteria
Adult over 18 Years old	Cognitive ability not suitable for the use of technologic tools.
Diagnosis: Ischemic heart disease in New York Heart Association (NYHA) functional class I-II with preserved global systolic function or in intermediate range (LVEF > 40%) after revascularized acute coronary syndrome.	
Lives in Melilla during the research period.	Absolute or relative contraindications to exercise testing
To have mobile technology with an internet connection at home (including one of the following devices: desktop personal computer, laptop, tablet, or smartphone)	
Ability and knowledge to access email or instant messaging	

Abbreviations LVEF, Left ventricular ejection Fraction.

**Table 2 ijerph-18-04038-t002:** Primary and secondary outcomes.

	Definition	Type
Primary Outcomes		
Biochemical	Hematies Level, Glucose, Creatine Kinase (CK), Triglycerides, Total Cholesterol, High Density Lipoprotein Cholesterol (HDL-C), Low Density Lipoprotein Cholesterol (LDL-C), Glycated Hemoglobin (HbA1c)	Clinical
Cardiac Function	Metabolic Equivalent (MET), Resting Heart Rate (RHR), Maximum Heart Rate (HRmax), Final Heart Rate (FHR), Rating Scale for Perceived Exertion (RPE), Systolic Blood Pressure (SBP), Diastolic Blood Pressure (DBP)	Clinical
Quality of Life	SF-12, EQ-5D	Self-Reported
Functional Capacity	Duke Activity Status Index (DASI)	Self-Reported
Secondary Outcomes		
Feasibility, Satisfaction and Usefulness	Telemedicine Satisfaction and usefulness Questionaire (TSUQ)	Self-Reported
Cost-Effectiveness	Direct Costs/Indirect Costs	€/Self-Reported
Adherence and Safety	Nº of sessions completed and adverse events record	Automatized App record

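### With prescribing left open and only a before/after comparison, changes in lipids, glucose, HbA1c, blood pressure and heart rate cannot be credited to CTR, so the article's claim of proof goes too far

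*Protocol article*

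**What the plan says.** Section 2 of the protocol article states that "all medical management, including medication prescription, will be at the discretion of the treating physician", and continues: "All changes will be documented and considered during analysis". Section 2.2 describes one route for participants: "Participants are assigned to the cardiac telerehabilitation group to receive an initial assessment". It also says that, at study start, "advice is given on general care, in physical activity and issues concerning drug intake". Section 2.5 gives the contrast, "The outcome measures will be compared before and after the completion of the 8-week CTR program", and the threshold, "Statistical significance was set at *p* < 0.05". It names neither a comparator nor a medication covariate or stratum.

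Table 2 lists four primary dimensions. Biochemistry has eight measures, ergometry (cardiac function) has seven, and the other two are quality of life (SF-12, EQ-5D) and functional capacity (DASI). Table 1 admits patients "after revascularized acute coronary syndrome" and gives no minimum interval since the event.

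Section 3 then states: "If the results confirm beneficial effects in biochemical, cardiac function, quality of live, and functional capacity, the effectiveness of the intervention will be proven".

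**The concern.** Open prescribing is ordinary in a study that runs alongside routine care. In a trial with a concurrent arm it does little harm, because both arms experience the same kind of drug changes and the difference between arms removes them on average. Here nothing removes them. If a lipid-lowering, glucose-lowering, antihypertensive or rate-limiting drug is started, stopped or re-dosed between T0 and T1, its effect enters the before/after difference alongside any effect of CTR.

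This affects most of two of the four primary dimensions. At stake is whether a fall in, say, LDL-C or systolic pressure can be read as evidence for the programme, and whether Section 3 may speak of proof.

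**Working it through.** **Step 1. Is there a concurrent group?** The study is labelled controlled, and the cost paragraph in Section 2.3.2 mentions sessions in both groups. But Section 2.2 assigns participants to CTR, Section 2.5 compares before with after, and the Discussion leaves comparison groups to future research. No second group is described.

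**Step 2. How many primary measures can drugs move directly?** From Table 2:
- Biochemical, 6 of 8: glucose, triglycerides, total cholesterol, HDL-C, LDL-C, HbA1c (not red cells or CK).
- Ergometry, 5 of 7: resting, maximum and final heart rate, SBP, DBP (not MET or perceived exertion).
- Total: 6 + 5 = 11 of 8 + 7 = 15.

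Section 2.2 itself recognises one such effect, noting that beta-blockers keep these patients below their maximum heart rate.

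**Step 3. How large could the effect be?** The article gives n = 30 without effect size, SD or power, so there is no figure of its own to reproduce. It also says nothing about how often drugs change or by how much.

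Assumptions:
- All 30 patients complete, and the true CTR effect is zero.
- The test is a paired t-test, two-sided at 0.05 (sidedness is not stated).
- A fraction f of patients has a drug change that shifts the outcome by k, all in one direction. The unit of k is the SD of the change score among patients without a drug change.

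Formulas:
- Mean shift = f × k
- SD of change in the mixed sample = √(1 + f(1 − f)k²)
- Standardised shift d = f × k / √(1 + f(1 − f)k²)
- Noncentrality = d × √30 = 5.477 × d, with 29 degrees of freedom and critical t = 2.045

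| f | k | d | Noncentrality | Chance of p < 0.05 |
|---|---|---|---|---|
| 10% | 0.5 | 0.05/√1.0225 = 0.049 | 0.27 | 5.8% |
| 20% | 1 | 0.20/√1.16 = 0.186 | 1.02 | 16.6% |
| 30% | 1 | 0.30/√1.21 = 0.273 | 1.49 | 30.3% |
| 50% | 1 | 0.50/√1.25 = 0.447 | 2.45 | 65.8% |

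The nominal rate is 5%. An observed mean change of 2.045/√30 = 0.37 SD is already significant.

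**Step 4. Does the missing comparator explain it?** In 20,000 simulated trials, the uncontrolled test was significant in 16.1%, 30.9% and 65.5% of runs for the last three rows. A hypothetical 15 + 15 comparison with the same drug changes in both arms gave 5.0%, 4.9% and 5.2%. The excess therefore arises because open prescribing is combined with a single group.

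**Step 5. Does this meet the Section 3 condition?** That sentence names four domains together. Drug changes can supply the biochemical domain and much of the cardiac-function domain. They would not by themselves necessarily improve SF-12, EQ-5D and DASI.

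**The case against.** The strongest reply is that the article has already dealt with this. Section 2 promises that changes will be documented and considered, and the exact method may stand in an analysis plan that is not shown. This stands in part. A reader might infer that drug changes will be ignored, or that the analysis will be an unadjusted difference. The article does not say so, and the lack of a detailed adjustment rule in a condensed article is not a fault in itself. What the reply does not reach is Section 3. With 30 patients and no comparator, no handling of recorded drug changes can turn the before/after difference into proof.

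A reader might also infer that drug titration alone could produce the proven result. The text does not support that, because the condition joins all four domains (Step 5).

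Third, the size and direction of the bias are assumed. The table takes every shift in one direction, and de-escalation would offset some of it. A reader might expect drugs to be intensified after an acute coronary syndrome. The article does not say so, and Section 2.1 describes low-risk class I patients and excludes those with earlier non-mild cardiac events. If changes are rare and small, the distortion is negligible, as the first row shows.

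Fourth, the drug-intake advice is weak evidence of bias. The Introduction lists better compliance with drug treatment among the ways rehabilitation works, so improved drug-taking is arguably part of the intended effect.

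Finally, the root problem is the missing comparator. That is so; open prescribing is one concrete route by which it affects the primary outcomes.

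**Conclusion.** The point holds in a limited form. The stated design cannot separate a CTR effect from concurrent drug changes for 11 of the 15 biochemical and ergometry measures. The promise to consider such changes is real but does not license the conclusion in Section 3. Drug changes could account for two of the four supports of that conclusion, one wholly and one largely; the documents do not show that they could account for all four.

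The mechanism is certain and the size is not. Under the assumptions above, the false-positive chance on one such outcome runs from about 6% to about 66%, depending on how many patients change drugs and by how much. The documented changes will show which end of that range applies. No direction of bias can be claimed from the article.

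**What to change.** 1. In Section 2.5, say how the documented changes will be used. Report each biochemical, blood-pressure and heart-rate outcome for all patients. As a supporting analysis, also report it for patients with no start, stop or dose change, between T0 and T1, of a drug acting on that outcome. State how many patients fall in each set.
2. In Section 3, replace the claim of proof with wording such as: *improvement in these domains will be described as change under CTR plus usual medical care, and will inform the design of a controlled trial.*

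The cost is wording and a few extra tables. No new data are needed, since Section 2 already commits to documenting the changes.

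The unchanged-drug set will be smaller than 30 and is defined after baseline, so its intervals will be wide and it can only support the main result. It leaves natural recovery and regression to the mean in place, and it does not capture changes in how well patients take drugs whose prescription stays the same. Only a concurrent comparator would address these.
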